### 2.7. Outcomes

All study participants will be evaluated before starting treatment (baseline) at 15 sessions and 30 sessions. The outcome measures are compiled in Table 3. 

The parameters of balance in sitting and standing static and dynamic and in the temporospatial and kinematic parameters of gait will be obtained from the following tests and scales. 

For static balance and functional mobility, the PASS Spanish version [21,45], the BBS [34] and the BESTtest [46] have been used. 

BBS has a high relative reliability with interrater reliability estimated at 0.97 (95% CI 0.96 to 0.98) and intra-rater reliability estimated at 0.98 (95% CI 0.97 to 0.99). The absolute reliability of the BBS varies across the scale, with minimal detectable change with 95% confidence varying between 2.8/56 and 6.6/56 [41].

PASS is a 12 items performance-based scale used for assessing and monitoring postural control following a stroke. It consists of a 4-point scale where three items are scored from 0 to 3, and the total scoring ranges from 0 to 36 [45]. The minimal detectable change in subacute stroke is 2.22 points [47]; in acute stroke, 1.8 points [48]; and in chronic stroke, it is 3.2 points [49].

BESTest consists of 27 tasks, with 36 items in total. Each item is scored based on ordinal scale scoring from 0 to 3, where 3 represents best performances, and 0 represents worst performances. Scores for the total test are provided as a percentage of total points [50]. Additionally, the minimal detectable change in subacute stroke is 7.81 points [50]. 

To measure dynamic balance and gait, the TUG test [51] and the 10 m walk test [52] will be used. 

In the TUG test, the patient rises from a chair, walks three meters in a straight line, turns, returns and sits down while the examiner times the time required to perform the test. In addition, the TUG assesses the risk of falling. A score of less than 10 s indicates a low risk of falling, between 10 and 20 s indicates frailty with a higher risk of falling, and more than 20 s a high risk of falling [51]. The minimum detectable change in stroke is estimated at 2.9 s [53].

10 m walk test has an excellent interrater reliability estimated ICC = 0.87 to 0.88, and an excellent interrater reliability ICC = 0.998. The minimum detectable change is set at 0.05m/s, and a substantial change is set at 0.10m/s [52].

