### 2.11. Data Management and Statistical Analysis

Sample size: For instance, to achieve 80% power to detect differences in contrast to the null hypothesis H₀, mean difference in BESTest is equal to the limit of superiority, using a one-sided Student’s t-Test (superiority) for two independent samples, taking into account that the significance level is 5%, and assuming that the superiority limit is 7.81 units, as suggested in the article by Candance, et al., [55]. Additionally, the proportion of patients in the control group with respect to the total is 50%; it will be necessary to include 18 patients in the control group and 18 in the experimental group, a total of 36 patients in this study. Considering that the expected percentage of dropouts is 20%, it would be necessary to recruit 22 patients in the control group and 22 patients in the experimental group, a total of 44 patients in this study.

Patient characteristics and comparisons at baseline: To assess the comparability of the two groups, the characteristics of the patients assigned to each group will be presented in a table. Discrete variables will be summarized as frequencies and percentages. Continuous variables and time intervals will be summarized using means, standard deviation, or median and interquartile range. Both groups need to be homogeneous at baseline.

The statistical analysis will be carried out by an intention-to-treat analysis.

Analysis of the main objectives: Normality tests of the dependent variables were undertaken using the Kolmogorov–Smirnov test. The description of the results of the dependent variables was also performed, using either the mean and the standard deviation or the median and interquartile range, depending on the adjustment of these variables to normality. 

To respond to the main objective, with each primary result, hypothesis tests will be performed (where the alternative hypothesis is the greater efficacy of the experimental treatment compared to the conventional one), and estimates will be provided by 95% confidence intervals. In addition, the t-Student test will be used for independent samples in the parametric case and the Mann–Whitney U test for the non-parametric case.

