Analysis of the secondary outcomes: For quality of life, contrasts of hypotheses will be made, and estimates will be provided by a 95% confidence interval. Furthermore, it is of interest to establish a regression model between quality of life and static balance, functional mobility, dynamic balance and gait in order to estimate their possible relationships. The strength of these relationships will be measured through the ANOVA F-test and the individual t-test. The strength of the relationship will be expressed as ORs and their 95% CI.

This project takes into account qualitative information to explore the reasons for possible dropouts through direct follow-up of patients.

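### The quality-of-life regression measures strength of relationship by F- and t-tests and then by odds ratios; the tests do not measure strength, and the odds ratios do not fit the model they come from

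*Protocol article*

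**What the plan says.** Protocol article, section 2.11 (analysis of the secondary outcomes), expresses the wish to "establish a regression model between quality of life and static balance, functional mobility, dynamic balance and gait in order to estimate their possible relationships". Two sentences then say how strength is to be judged:

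- The first names tests: "The strength of these relationships will be measured through the ANOVA F-test and the individual t-test".
- The second, directly after it, names an effect measure: "The strength of the relationship will be expressed as ORs and their 95% CI".

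The regression paragraph names domains, not instruments. Section 2.7 links instruments to domains, first for the static domain: "For static balance and functional mobility, the PASS Spanish version [21,45], the BBS [34] and the BESTtest [46] have been used". It then does so for the dynamic domain: "To measure dynamic balance and gait, the TUG test [51] and the 10 m walk test [52] will be used". Table 3 places two instruments in each of two domains (PASS and BESTest; 10 m walk and TUG) and does not list the BBS. Section 2.11 sizes the trial at "a total of 36 patients in this study", raised to 44 for dropout.

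**The concern.** The stated purpose is estimation: "in order to estimate their possible relationships". Neither sentence on strength serves it.

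First, F and t measure evidence against a null hypothesis. For a relationship of fixed strength they increase with sample size, so they cannot express how strong it is.

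Second, an overall F-test with individual coefficient t-tests is the output of a linear model for a continuous outcome, whose natural effect measure is a slope. An odds ratio comes from a logistic-type model for a categorical outcome. The two sentences describe different models.

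Third, the pairing of an overall F with individual t-tests points to one joint model. There, each t-test's null is that the predictor adds nothing once the others are included, not that quality of life is unrelated to it. The two nulls differ most when predictors overlap, as scales of the same domain can be expected to do.

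At stake is how this part of the secondary analysis is read. A p-value could be reported as strength, or a scale could appear unrelated to quality of life because a sister scale is in the same model. The Discussion itself treats static and dynamic balance as a key determinant of quality of life.

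**Working it through.** **Inputs.** From section 2.11: N = 36 evaluable, 44 recruited. From section 2.7 and Table 3: 4 instruments (5 with the BBS). Assumed, because the document gives none: correlation of each scale with quality of life r = 0.4 to 0.6; correlation between scales ρ = 0.3 to 0.9, equal for all pairs; two-sided 5% tests. The plan states no sample size, power or correlation for this regression, so there is no figure of its own to reproduce.

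**Step 1: F and t are not measures of strength.** For one predictor, t = r·√[(N−2)/(1−r²)]. With r = 0.5 in both cases:

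- N = 36: t = 0.5·√(34/0.75) = 3.37
- N = 44: t = 0.5·√(42/0.75) = 3.74

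For the overall test, F = (R²/k) / [(1−R²)/(N−k−1)]. With k = 5 and R² = 0.298 in both cases:

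- N = 36: F = 0.0596/(0.702/30) = 2.55
- N = 44: F = 0.0596/(0.702/38) = 3.23

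The relationship is the same, but the statistics differ. This step does not depend on which predictors are chosen.

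**Step 2: the two sentences on strength, side by side.** Sentence one: F and t, so a linear model, reported as slopes. Sentence two: odds ratios, so a categorical outcome and a logistic-type model. One model does not yield both.

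**Step 3: what the individual t-test detects.** With k equally correlated predictors:

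- partial slope b = r/[1+(k−1)ρ]
- R² = k·r²/[1+(k−1)ρ]
- variance inflation VIF = [1+(k−2)ρ] / {(1−ρ)[1+(k−1)ρ]}
- noncentrality δ ≈ b·√{N/[VIF·(1−R²)]}

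Examples at N = 36, r = 0.5:

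- **Scale alone:** δ = 0.5·√(36/0.75) = 3.46; power about 90% (89% in simulation).
- **k = 5, ρ = 0.8:** b = 0.5/4.2 = 0.119; R² = 1.25/4.2 = 0.298; VIF = 3.4/(0.2·4.2) = 4.05; δ = 0.119·√[36/(4.05·0.702)] = 0.42; power about 7%.
- **k = 5, ρ = 0.5:** b = 0.5/3 = 0.167; R² = 1.25/3 = 0.417; VIF = 2.5/(0.5·3) = 1.67; δ = 0.167·√[36/(1.67·0.583)] = 1.01; power about 15%.
- **k = 2, ρ = 0.5:** b = 0.5/1.5 = 0.333; R² = 0.5/1.5 = 0.333; VIF = 1/(1−0.25) = 1.33; δ = 0.333·√[36/(1.33·0.667)] = 2.12; power about 50%.

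Simulation over r = 0.4 to 0.6, N = 36:

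| Predictors | ρ | Each t-test | Overall F |
|---|---|---|---|
| 4–5 | 0.7–0.9 | 5–15% | 45–98% |
| 4–5 | 0.5 | 10–35% | 69–100% |
| 4–5 | 0.3 | 20–87% | 87–100% |
| 2 | 0.5–0.7 | 19–76% | 67–100% |

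The same scale entered alone is significant in 68 to 98% of runs. In the first row, when F is significant, no individual t-test is significant in about 47 to 75% of runs. With all 44 patients, the t-test in the first-row setting still reaches only about 6 to 17%.

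**The case against.** The strongest defence is that the paragraph names domains, not scales. It does not say that several instruments of one domain enter together, and one instrument per domain fits the wording too. The choice of predictors is commonly left to an analysis plan, which is not shown here. This stands: joint entry of overlapping scales is a likely inference from section 2.7 and Table 3, not a stated fact.

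A reader might go further and infer that real relationships will mostly be declared absent. The document does not support that. It plans the overall F-test as well, which mostly keeps its power. It has no rule that a non-significant t-test means no relationship. The power loss also rests on correlations the document does not give. In addition, where scales correlate 0.8 to 0.9, each adds little beyond the others under the simulated structure, so a non-significant partial t-test is mostly the right answer to the question it asks. Multiple regression is a legitimate method, and preferring separate models is partly a matter of choice.

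The defence does not reach the first two parts of the concern. Whatever predictors enter, F and t do not measure strength. The odds-ratio sentence does not repair this, because it names an effect measure from a different kind of model.

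**Conclusion.** The point holds in a limited form. Two errors are in the text and need no assumption: strength is to be measured by test statistics, and it is to be expressed in odds ratios that the stated model does not yield.

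The third part is conditional. If 4 to 5 strongly overlapping scales enter one model with about 36 patients, the individual t-tests would be close to uninformative about each scale's own relationship with quality of life. That rests on the assumed inter-scale correlations of 0.7 to 0.9. Individual power is much better with weaker overlap, or with two predictors correlated 0.5 to 0.7, though wide ranges remain. The global F-test would usually still detect a joint relationship, but it cannot say which one, and the plan wants to estimate them all.

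Severity is minor. The paragraph presents the regression as of interest, it is not among the objectives at the end of the Introduction, and no comparison between arms depends on it.

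**What to change.** Replace both sentences, the one on F- and t-tests and the one on odds ratios; changing only the first would leave the text contradicting itself. Suggested wording:

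> *The association of ECVI-38 with each balance and gait measure will be estimated in a separate linear model per instrument at a given visit, with treatment arm as a covariate, and reported as the standardised slope and R-squared with 95% CI; F- and t-tests serve only as tests. Any joint model will use one instrument per domain, and a non-significant individual t-test in it will not be read as no relationship.*

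The cost is a change of wording and a few more exploratory models, with no new data or patients. The downside is that per-instrument models do not show what each scale contributes independently of the others.

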## Abstract

Background: Many stroke survivors suffer from sensorimotor deficits, especially balance impairments. The purpose of this trial is to investigate whether the designed Immersive Virtual Reality training program is better in the short term (15 sessions) and in the medium term (30 sessions) than physiotherapy training with Bayouk, Boucher and Leroux exercises, with respect to static balance in sitting and standing, dynamic balance and quality of life in patients with balance impairment in stroke survivors. Methods: This study is a randomized controlled trial with two treatment arms and evaluators blinded, and a functionality treatment group in combination with specific balance exercise training according to Bayouk, Boucher and Leroux (control group) or a balanced treatment using Immersive VR. The primary outcome will be static, Dynamic balance and gait measured by Bestest Assessment Score (BESTest), Berg Scale (BBS), Pass Scale (PASS) and Time Up and Go test (TUG). The secondary outcome will be the stroke-associated quality of life using the Stroke Quality of Life Scale (ECVI-38). Conclusions: The results of this study may add new insights into how to address balance using Immersive Virtual Reality after a stroke. If the new training approach proves effective, the results may provide insight into how to design more comprehensive protocols in the future for people with balance impairments after stroke.

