The secondary outcomes will be measured with the following tools: quality of life with the ECVI-38 [54] and the adverse effects with a notebook for recording if they happen derived from the treatment.

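### Section 2.11 promises odds ratios from a regression of the ECVI-38 score that is tested with F and t statistics; a linear model of a scale score gives no odds ratio.

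*Protocol article*

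**What the plan says.** The paragraph on secondary outcomes in section 2.11 (Data Management and Statistical Analysis) first plans hypothesis tests and 95% confidence intervals for quality of life. It then adds a second analysis: "it is of interest to establish a regression model between quality of life and static balance, functional mobility, dynamic balance and gait". Two sentences describe how that model will be judged and reported:

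- Tests: "The strength of these relationships will be measured through the ANOVA F-test and the individual t-test".
- Effect measure: "The strength of the relationship will be expressed as ORs and their 95% CI".

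Quality of life is defined by instrument only. Section 2.7 (Outcomes) gives the secondary measures as "quality of life with the ECVI-38 [54] and the adverse effects with a notebook for recording", and the Abstract and Table 3 likewise name the ECVI-38 without any cut-off, responder definition or ordered categories.

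**The concern.** The tests and the effect measure belong to different models. An overall ANOVA F-test with a t-test for each coefficient is the usual inference for least-squares linear regression of a quantitative outcome. An odds ratio comes from a logistic or ordinal model of a categorical outcome, normally tested with Wald or likelihood-ratio chi-square statistics.

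An analyst who follows the text literally has two ways to produce something called an odds ratio. One is to exponentiate linear slopes, which gives numbers that are not odds ratios. The other is to categorise the ECVI-38 at a threshold that the article does not state and fit a model that it does not name. What is at stake is whether the reported association can be interpreted, and whether its reporting scale is settled before the data are seen.

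**Working it through.** There is no stated figure to reproduce. The check compares the statements with each other and with the definitions of the variables.

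**1. Which model do the tests imply?** Section 2.11 does not use the word linear. But a scale score as outcome, an ANOVA F-test for the whole model and a t-test per term together describe

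ECVI-38 = b0 + b1·x1 + … + bk·xk + error,

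where each b is the mean difference in ECVI-38 points per unit of the measure x. No odds appear in this model.

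**2. Is there a categorical ECVI-38 anywhere?** The Abstract, section 2.7, Table 3 and section 2.11 were checked. None gives a cut-off, a responder definition or ordered categories, and none names a logistic or ordinal model.

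**3. Does reversing the regression help?** The wording of the relationship is loose about direction, so quality of life could be read as the predictor. The other variables are quantitative too:

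| Measure | Scale in section 2.7 |
|---|---|
| BESTest | "Scores for the total test are provided as a percentage of total points" |
| PASS | total from 0 to 36 |
| TUG | seconds |
| 10 m walk test | change given in m/s |

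The only bands given are those for TUG (under 10 s, 10 to 20 s, over 20 s). They describe fall risk and are not named as a regression outcome. Neither direction yields an odds ratio.

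**4. What happens if slopes are exponentiated?** The following uses simulated data, not trial data: 36 subjects, four predictors and a continuous outcome.

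- Least squares gave an overall F of 2.85, a t statistic per coefficient, and a first slope of 4.489 outcome points per predictor unit.
- exp(4.489) = 89.0, which is not the odds of anything.
- If the same outcome is expressed on a scale one tenth as long, the slope becomes 4.489/10 = 0.4489 and exp(0.4489) = 1.57. The fit is identical, yet the supposed odds ratio moves from 89.0 to 1.57 because the outcome's unit changed.
- A logistic fit to the same continuous outcome was rejected by the software, because that model needs an outcome between 0 and 1.

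The numbers illustrate the mechanism only and do not estimate any quantity in this trial.

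**The case against.** The strongest reply is that this matters little. The regression is introduced as something of interest, to estimate possible relationships. It is an association model, not a treatment comparison. The secondary objectives in the Introduction are the impact on quality of life and safety, and this regression addresses neither directly. The between-group quality-of-life analysis is a separate sentence with its own confidence interval and no odds ratio, and the sample size rests on the BESTest. All of this stands and limits the weight of the point. It does not remove the contradiction between two adjacent sentences.

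It could also be said that the full protocol or a statistical analysis plan may contain a cut-off. That is possible, but the point is not that a detail is missing. The article states an effect measure that conflicts with the tests it states, and a cut-off elsewhere would still leave the F and t tests out of place.

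Two stronger readings are tempting and are not supported:

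- A reader might infer that the analysis cannot be carried out at all. The linear regression with its F and t tests can be run; only the odds ratio is unavailable from it.
- A reader might infer that the trial will dichotomise the ECVI-38 after seeing the data, with loss of information and an overfitted logistic model. The article never mentions dichotomising. Events-per-predictor or efficiency figures would therefore describe a model that is not in the document, and they would need assumptions about the ECVI-38 distribution that the article does not allow one to check.

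It might also be objected that F and t statistics measure evidence, not strength of relationship. That is mainly wording: at fixed degrees of freedom the overall F is a one-to-one function of R-squared. It is not a separate defect.

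**Conclusion.** The point holds as an internal mismatch: the odds ratios stated in section 2.11 cannot come from the model that the same paragraph describes. The conclusion rests on reading the F-test and t-tests as linear regression, which is an inference but the natural one for a scale score, and on the absence from the article of any categorical ECVI-38 outcome or logistic model.

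The size is limited. One sentence is wrong, in an exploratory secondary analysis, and no figure in the article changes. The primary comparison, the between-group comparison of quality of life and the sample size are untouched. It should still be corrected, because otherwise the reported association would be either uninterpretable or dependent on a cut-off that the article does not fix.

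**What to change.** Replace the odds-ratio sentence in the secondary-outcomes paragraph of section 2.11 with:

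*The relationships will be expressed as linear regression coefficients (difference in ECVI-38 score per unit of each measure) with 95% CI, and R-squared for the model.*

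Keep the ECVI-38 as a score, without dichotomising it. The existing F and t tests then fit the model and can stay. Removing the contradiction does not require further covariates or rescaling by minimal detectable change; the latter would not be unique in any case, since section 2.7 gives three values for PASS (2.22, 1.8 and 3.2 points) and a range for the BBS (2.8 to 6.6).

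If the investigators do want odds ratios, the alternative is to pre-specify ECVI-38 categories and a logistic or ordinal model, and to replace the F and t tests with tests that suit it. The first option is simpler and uses the whole score.

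The cost is one sentence. No additional data, patients or assessments are needed.

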This study aims to determine whether the designed Immersive VR training program is better in the short term (15 sessions) and medium term (30 sessions) than physiotherapy training with exercises by Bayouk, Boucher and Leroux [39] regarding the change of measures related to static sitting, and standing balance and dynamic balance in post-stroke patients.

Secondary objectives verify the impact on quality of life and safety of the application of this type of technology.

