### 2.5. Physiotherapists Training

The interventions in both groups will be carried out by 4 physiotherapists with at least 5 years of experience in patients post-stroke management. In addition, physiotherapists will attend a 2 h training session to improve the standardization of interventions and receive a detailed procedure for each intervention to ensure they are managing patients according to trial protocols as well as recording adverse events if required. 

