**Figure 3 healthcare-11-01335-f003:**
[figure not shown]
Immersive Virtual Reality scenarios.

**Table 1 healthcare-11-01335-t001:** Protocol of intervention.

Intervention Protocol	
Control Group (CG)	Intervention Group (IG)
15 min: physiotherapy treatment aimed at achieving functional improvement and increased postural control [44].	15 min: physiotherapy treatment aimed at achieving functional improvement and increased postural control [44].
15 min: static and dynamic balance training in sitting and standing according to Bayouk, Boucher and Leroux protocol [39].	15 min: static and dynamic balance training in sitting and standing through Immersive VR.

**Table 2 healthcare-11-01335-t002:** Exercises of the protocol of Bayouk, Boucher and Leroux (control group).

Exercises	Repetitions	Total Time
Stand with feet together for 10 s.	8 repetitions	2 min
Hold the tandem posture for 10 s.	8 repetitions	2 min
Get up from the chair without using arms.	3 sets of 8 repetitions	3 min
Walk forwards and backwards with one foot in front of the other.		5 min
Stay in monopodal support for 10 s.	10 repetitions	3 min

**Table 3 healthcare-11-01335-t003:** Outcomes measures.

Outcome Domain	Measures Instrument	T0	T1	T2
Sociodemographic and descriptive data	Ad Hoc questionnaire	X		
Primary outcomes				
Static balance and functional mobility	PASS	X	X	X
	BESTtest	X	X	X
Dynamic balance and gait	10 m walk test	X	X	X
	TUG	X	X	X
Secondary outcomes				
Quality of life	ECVI-38	X	X	X
Adverse effects	Open questions		X	X

T0 baseline, T1 evaluation at 15 sessions, T2 evaluation at 30 sessions. PASS- Postural Scale for Stroke Patients; TUG- Timed Up and Go; BESTest- Balance Evaluation System Test; ECVI-38- Quality of life scale for stroke.

**Table 4 healthcare-11-01335-t004:** Study period: Schedule of enrollment, interventions and assessments of this study.

STUDY PERIOD					
	Enrolment	Allocation	Post-Allocation		Closeout
Time points baseline	t	0	t15	t30	tx
Enrollment					
Eligibility screen	X				
Informed consent	X				
Allocation		X			
Assessments					
Baseline variables		X			
Post. Intervention and follow-up variables			X	X	X
Interventions					
IVR training group			X	X	
Physical therapy with Bayouk, Boucher and Leroux exercises			X	X	

IVR: Virtual Reality intervention group.

**Table 5 healthcare-11-01335-t005:** Collection of sociodemographic and descriptive data.

**Sociodemographic and descriptive data**	Age	Years
	Gender	Male/female
	BMI	Underweight/normal weight/overweight

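### The adverse-effect questions are scheduled only at 15 and 30 sessions, so patients who stop before session 15 are covered by event-driven recording alone, and the planned dropout contact is not linked to the adverse-effect outcome

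*Protocol article*

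**What the plan says.** The Introduction of the Protocol article makes safety an objective: "Secondary objectives verify the impact on quality of life and safety of the application of this type of technology".

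Adverse-effect collection is described in three places:

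- **Table 3** gives the instrument and its times as "Adverse effects Open questions X X". The T0 cell is empty, and the table note defines the other two as "T1 evaluation at 15 sessions, T2 evaluation at 30 sessions". Section 2.10 gives baseline, 15 and 30 sessions as the general times for outcome measures.
- **Section 2.7** names a different instrument: "the adverse effects with a notebook for recording if they happen derived from the treatment". It sets no visit limit.
- **Section 2.5** trains the treating physiotherapists so that they are "managing patients according to trial protocols as well as recording adverse events if required". Section 2.9 says these staff are not blinded to allocation.

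On dropout, Section 2.11 expects 20% and states: "This project takes into account qualitative information to explore the reasons for possible dropouts through direct follow-up of patients". For the secondary outcomes the same section names an analysis of quality of life ("For quality of life, contrasts of hypotheses will be made, and estimates will be provided by a 95% confidence interval"). It names none for adverse effects.

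**The concern.** Open questions put to every patient at a fixed time are solicited ascertainment. A notebook used when something happens is event-driven: it depends on the patient volunteering a symptom, on staff noticing it, and, as Section 2.7 words it, on the effect being judged to come from treatment. Patients who reach T1 get both. Patients who stop before T1 get only the second.

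People who stop because they felt unwell are not a random subset, so the weaker method falls on a group in which adverse effects may be over-represented. A symptom felt after a session, by a patient who then declines to continue, might first be disclosed when the trial asks why they stopped. That contact is planned, but the article does not say that its content reaches the adverse-effect outcome. What is at stake is how far the trial's statement on the safety of the VR training can be relied on.

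**Working it through.** No stated figure is in dispute, so the check sets the passages side by side.

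**1. Who is asked, and when**

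| Patient | Open questions (Table 3) | Notebook and physiotherapist recording (2.7, 2.5) | Dropout contact (2.11) |
|---|---|---|---|
| Completes 30 sessions | T1 and T2 | yes | not applicable |
| Stops between sessions 15 and 30 | T1 | yes | planned |
| Stops before session 15 | none scheduled | yes, while in treatment | planned |

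At 5 sessions a week (Section 2.6), T1 falls after 15 / 5 = 3 weeks of treatment. The unsolicited window is therefore the first three weeks.

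**2. Which source feeds the outcome**

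Table 3 names "Open questions" as the instrument and does not list the notebook. Section 2.7 names the notebook and does not mention the questions. The article does not say whether the outcome is built from one, the other or both.

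**3. Whether the dropout contact feeds the outcome**

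Section 2.11 calls the information qualitative. It states neither a link to the adverse-effect outcome nor a separation from it.

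**4. Scale**

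- Inputs: 22 recruited per arm and 20% expected dropout, both from Section 2.11.
- Expected dropouts: 0.20 × 22 = 4.4 per arm, or 0.20 × 44 = 8.8 in total.
- The article does not say how many would stop before session 15, how many because of an adverse effect, or how many such events the notebook would miss.

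Let k be the number of VR patients who stop before session 15 because of an adverse effect that reaches the trial only at the dropout contact. If that contact is not counted, the VR proportion over all 22 randomised is too low by k / 22:

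- k = 0: 0 / 22 = 0%
- k = 2: 2 / 22 = 9.1%
- k = 4: 4 / 22 = 18.2%

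The values of k are assumptions. The last needs nearly all of the 4.4 expected dropouts to be early, caused by an adverse effect and missed by the notebook, so it is an outer bound and not a forecast.

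**The case against.** The strongest reply is that most of the gap is already covered. The notebook has no visit limit. The physiotherapists see patients five days a week and have a detailed procedure. Dizziness that ends treatment at an early session is just what an event-driven record should catch. The full protocol may also hold detailed safety rules that a journal article leaves out. Table 4 adds a closeout point (tx) for follow-up variables, which might reach some dropouts, although Table 3 does not carry it.

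Much of this stands. It means that the loss is partial and cannot be sized. It does not remove the difference in method: the published schedule gives solicited questions to those who reach T1 and only event-driven recording, by staff who know the allocation, to those who do not.

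A reader might go further and infer three things that the article does not support:

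- **That dropout reasons are kept out of the adverse-effect outcome.** Section 2.11 does not say so. It is only silent on a link.
- **That the safety result becomes a comparison of patients who tolerated 15 sessions.** No safety denominator or between-group safety analysis is described, and the stated analysis principle is intention to treat.
- **That the loss runs in one direction, in favour of VR.** Headset intolerance can arise only in the VR arm. But control patients do tandem and single-leg stance, with eyes closed and on soft surfaces (Section 2.6, Table 2). They too may have adverse effects and stop early, under the same recording routes.

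**Conclusion.** The point holds as a gap in ascertainment. By the article's own schedule, patients who stop before session 15 are never systematically asked about adverse effects. The article also describes collection differently in Table 3 and in Sections 2.5 and 2.7, and does not connect the dropout contact to the outcome. Adverse effects in early stoppers can therefore be under-recorded.

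The size cannot be derived. The range of 0 to 18.2 percentage points in the VR arm rests wholly on assumed counts of 0 to 4 missed patients, and the notebook should keep the true figure towards the low end. This is a change that should be made because it is cheap and safety is a stated objective. It is not evidence that the safety result will be wrong.

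**What to change.** 1. Reconcile Table 3 with Sections 2.5 and 2.7 by stating that notebook entries and open-question answers both feed the adverse-effect outcome.
2. Add a treatment-stop time point to the adverse-effects row of Table 3, and put the same open questions to the patient at the dropout contact already planned in Section 2.11. State that an adverse effect given as the reason for stopping counts in the outcome.
3. Report adverse effects, and stops due to adverse effects, by arm over all randomised patients (22 per arm as planned).

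The cost is one column in Table 3, a few sentences in Sections 2.7 and 2.11, and a little more recording. No extra visit or staff is needed. The safety figure may come out somewhat less favourable.
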